### Site and Provider Selection

The study will take place in public sector facilities in 2 Nigerian states, 1 in the north (Kaduna) and 1 in the south (Ondo). The north and south of Nigeria differ in religious beliefs, contraceptive prevalence rate, and availability of health care providers, making it necessary to generate evidence in each context. We will purposively select local government areas (LGAs) in Kaduna and Ondo States for study participation by excluding LGAs with overlapping interventions and, given the extensive supervision needs of the study, hard-to-reach LGAs.

Facilities will be eligible if they provide referral services on site or are located within 20 km of a referral facility, in case of adverse events resulting in the need to refer clients; if there is a provider interested in participating in the study who expects to be in the facility for the 12-month period of client recruitment; and if the facility has been providing FP in the previous 3 years and does not currently provide implants. Larger urban centers staffed by nurses, midwives, and CHEWs and smaller rural health centers staffed by a nurse or midwife only will be eligible for inclusion.

A total of 60 facilities will be selected in each state from eligible facilities, yielding a total of 120 facilities. Where there are more than the required number of eligible facilities, simple random sampling will be used to select facilities for inclusion. At least 30 nurse or midwife-led facilities will be selected in each state to allow inclusion of 30 nurses and midwives in the study. The remaining 30 facilities will include as many CHEW-led facilities as possible. From each CHEW-led facility, 1 CHEW will be trained, and 1 nurse or midwife or 1 CHEW will be trained from each nurse or midwife-led facility. The providers trained will be the individuals responsible for providing FP services at their facility.

**Table 1 table1:** Details of implant brands to be included in the study.

Product	Composition	Labeled duration of use	Format
Jadelle	150 mg levonorgestrel, 2 rods	5 years	2 rods, separate disposable trocar
Implanon Classic	68 mg etonorgestrel, 1 rod	3 years	1 rod preloaded in trocar

**Table 2 table2:** Implant insertion adverse events to be recorded.

Description of adverse reaction		Day recorded relative to procedure
Anaphylactic reaction to the implant		0
Implant insertion unsuccessful on first or second attempt		0
Implant breaks		0

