### Sample Size

#### Day of Insertion

Calculation of the number of participants required for the study is based on the primary outcome—the frequency of adverse events associated with insertion on the day of the procedure.

Studies documenting adverse events of implant insertion on the day of procedure have found them to be rare. For example, a randomized clinical trial of 2008 women found that 0.2% clients using Jadelle and 0.8% clients using Implanon Classic experienced complications at insertion [26].

To detect a difference in proportion of adverse events between the 2 study arms with a noninferiority limit of 0.5%, 80% power, and 95% confidence level on the day of implant insertion, we would require a sample size of 2462 in each study arm, giving a total sample size of 4924. To account for possible clustering, we will include a design effect of 1.5, increasing the sample size to 7386. To allow for incomplete records, we will increase this by 10% to a total sample size of 8125.

We estimate that each provider will receive approximately 10 insertion clients per month and that we may see a refusal rate of 20%. With a total of 120 providers, we expect to recruit 1200 clients per month. We would therefore need to recruit clients for approximately 7 months to achieve the required sample size for insertions.

#### By Day 14

We expect the number of adverse events observed by day 14 to be higher than that at day 0 as we may start to see infections. This reduces the required sample size needed to detect a difference between health care provider types. To detect a difference in proportion of adverse events between the 2 study arms with a noninferiority limit of 1%, 80% power, and 95% confidence level 14 days after implant insertion, we would require a sample size of 1225 in each study arm, giving a total sample size of 2450. To account for possible clustering, we will include a design effect of 1.5, making the size 3675. Assuming 20% loss to follow-up makes a total sample size of 4410. If we expect to recruit 1200 clients per month, it will take around 4 months to recruit the sample size we require.

All recruited clients will be asked to return to the inserting provider for a follow-up visit at 14 days post insertion until the sample size of 4410 is reached.

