#### Quality and Acceptability of Implant Provision

To detect a difference in the quality and acceptability of implant provision between the 2 study arms, assuming that each group would score an average of 80% of quality and acceptability indicators being met, with a noninferiority limit of 10%, 80% power, and a significance level of 5%, we will need 198 observations in each group. Adjusting for 10% incompleteness, we need 220 in each group (440 total). Assuming a design effect of 1.8 requires a minimum of a total of 792 observed implant insertions. There will be approximately 10 providers per supervisor. So, assuming approximately 10% of insertions can be observed (and client acceptability measured through exit interviews), this equals 812 insertions, which is sufficient according to the sample size calculation.

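### The day-14 target of 4410 covers a 16.7% loss to follow-up, not the stated 20%, and the forecast of 1200 recruits per month leaves out the stated 20% refusal

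*Protocol article*

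**What the plan says.** All references are to the protocol article, Methods.

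- **Sample Size, By Day 14.** 1225 per arm gives 2450, and a design effect of 1.5 gives 3675. Then: "Assuming 20% loss to follow-up makes a total sample size of 4410". The section goes on to say that recruiting this number at 1200 clients per month takes around 4 months.
- **Sample Size, Day of Insertion.** "we would require a sample size of 2462 in each study arm, giving a total sample size of 4924"; the design effect brings this to 7386. Then: "To allow for incomplete records, we will increase this by 10% to a total sample size of 8125".
- **Sample Size, Quality and Acceptability of Implant Provision.** From 198 per group: "Adjusting for 10% incompleteness, we need 220 in each group".
- **Accrual (Day of Insertion).** One sentence expects about 10 insertion clients per provider per month and a possible refusal rate of 20%. The next reads: "With a total of 120 providers, we expect to recruit 1200 clients per month". The conclusion is about 7 months, a figure that also appears under Participant Recruitment and Eligibility.
- **Site and Provider Selection.** A facility qualifies only if it has an interested provider who "expects to be in the facility for the 12-month period of client recruitment".

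**The concern.** If a fraction d of enrolled women is lost, the number to enrol is the required number divided by (1 − d). Multiplying by (1 + d) gives too few, and the gap widens as d grows. The day-14 figure uses the multiplied form. Data Analysis specifies complete case analysis, so women without a follow-up drop out and nothing makes up the difference. If losses ran exactly as planned, the day-14 comparison would miss the number the article says it needs.

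The accrual forecast has a different fault. A refusal rate is stated and then not used, so the monthly rate is too high and the recruitment period built on it too short.

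**Working it through.** **1. The day-14 figure**

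Inputs, all from By Day 14: 1225 per arm, design effect 1.5, loss 20%.

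- Required: 1225 × 2 × 1.5 = 3675.
- Stated total: 3675 × 1.2 = 4410, reproduced exactly.
- Loss that 4410 can absorb: 1 − 3675/4410 = 16.7%.
- Left after 20% loss: 4410 × 0.8 = 3528, which is 147 short (147/3675 = 4.0%).
- Enrolment that meets the stated loss: 3675/0.8 = 4593.75, so 4594. That is 184 more (184/4410 = 4.2%).

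**2. Effect on day-14 power**

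The article gives a 1% margin, 80% power and a 95% confidence level, but no event rate and no statement of a one- or two-sided calculation. Assume a 1% event rate in both arms and a one-sided 5% test:

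- n per arm = 2 × 0.01 × 0.99 × (1.645 + 0.842)² / 0.01² ≈ 1225, which matches the article.

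After 20% loss the effective number per arm is 3528/(2 × 1.5) = 1176.

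- Power = Φ(√(1176/1225) × (1.645 + 0.842) − 1.645) = 78.6%.

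This hardly depends on the assumption. If 1225 is instead taken to give 80% power at one-sided 2.5% (which implies an event rate of about 0.79%), the same shortfall gives 78.4%.

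**3. The other two allowances**

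| Sample | Before allowance | × (1 + d) | ÷ (1 − d) | Stated |
|---|---|---|---|---|
| Quality, d = 10% | 198 per group | 217.8 | 220 | 220 |
| Day 0, d = 10% | 7386 | 8124.6 | 8206.7 | 8125 |
| Day 14, d = 20% | 3675 | 4410 | 4593.75 | 4410 |

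The quality sample is divided; the two safety samples are multiplied. If 10% of day-0 records were incomplete, 8125 × 0.9 = 7312.5 would remain of 7386, about 1.0% short. On the matching assumption (0.5% event rate, one-sided 5%, giving 2461 per arm against the stated 2462), power is about 79.7%, a loss of about 0.3 points.

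**4. Accrual**

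Inputs from Day of Insertion: 120 providers, 10 clients each per month, 20% refusal.

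- Stated: 120 × 10 = 1200, reproduced only with refusal left out. 8125/1200 = 6.8 months; 4410/1200 = 3.7 months.
- With refusal: 120 × 10 × 0.8 = 960 per month. The stated rate is 1200/960 = 1.25 times this.
- Day 0: 8125/960 = 8.5 months, against about 7. Seven months at 960 gives 6720 clients.
- Day 14: 4410/960 = 4.6 months, or 4594/960 = 4.8 months, against about 4. Four months at 960 gives 3840 clients.

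**The case against.** **4410 might count completed follow-ups.** The abstract and Table 3 can be read that way, and By Day 14 keeps asking clients to return until 4410 is reached. On that reading 4410 exceeds 3675 and nothing is short. The derivation does not support it: the loss allowance is already inside 4410, and the next sentence gives the time to recruit that number. It is an enrolment figure. The telephone follow-up (three attempts before a woman counts as lost) may keep losses below 20%, but it does not make the stated sum right.

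**Day 0 is not a plain error.** The text openly says it increases the number by 10% and gives no incompleteness rate. This largely stands. Day 0 is a minor instance of the inconsistency, not a failure against a stated assumption.

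**The 10 clients per month might already be net of refusal.** Women who decline are directed elsewhere, so this is possible. But the refusal rate in the same sentence would then serve no purpose, and it is the less natural reading.

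**Stronger readings a reader might infer.**
- *That power falls to 70% or below.* Such a figure comes from replacing one-sided 5% with one-sided 2.5% at the same event rates. That alone gives about 70.1% before any loss, so it says nothing about the loss allowance.
- *That the wrong duration disturbs supervision.* Under Quality of Implant Provision, visits are fixed at 0, 1, 2, 3 and 6 months after training, whatever the accrual.
- *That slow accrual shrinks the sample.* Recruitment continues until the target is reached.
- *That the refusal omission explains the actual recruitment period.* The Results section reports November 2015 to December 2016 and gives no cause.

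**Conclusion.** Two stated figures are wrong on the article's own assumptions.

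The first is the day-14 target, 184 below what a 20% loss requires. The cost is modest: about 1.4 points of power if losses reach 20%, and nothing if they stay at or below 16.7%. The shortfall of 147 women follows from the article's figures alone; the 78.6% rests on the assumed event rate and one-sided 5% level.

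The second is the accrual rate, overstated by 25%, which lengthens recruitment from about 7 to about 8.5 months. This is a planning error and does not alter the final number.

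The periods of 7 and 12 months also need reconciling. They may be an expected time to target and an outer window, and the corrected 8.5 months fits inside 12, but the article describes both as the time over which clients are recruited.

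**What to change.** - **Day-14 target.** Restate it as 4594. The extra 184 come from women already being enrolled towards 8125, so the cost would be their follow-up and travel reimbursement, with no added enrolment. As the Results section reports recruitment complete, the alternative is to keep 4410 and state that it covers a 16.7% loss and yields 3528 women (about 78.6% power on the assumptions above) at 20% loss. In either case, report the analysable day-14 number against 3675.
- **Day-0 target.** Optional: give 8207, or keep 8125 and say that it leaves about 7313 if 10% of records are incomplete.
- **Accrual.** In Sample Size, change 1200 to 960 clients per month, about 7 to about 8.5 months, and around 4 to about 4.6 months (4.8 for a target of 4594). Change the 7 months under Participant Recruitment and Eligibility to match. If the 10 clients per month were meant net of refusal, say so instead.
- **Recruitment period.** State how the 12 months under Site and Provider Selection relates to the expected time to target.

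With recruitment closed, these are text corrections and one reported number.

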#### Quality and Acceptability of Implant Provision

To detect a difference in the quality and acceptability of implant provision between the 2 study arms, assuming that each group would score an average of 80% of quality and acceptability indicators being met, with a noninferiority limit of 10%, 80% power, and a significance level of 5%, we will need 198 observations in each group. Adjusting for 10% incompleteness, we need 220 in each group (440 total). Assuming a design effect of 1.8 requires a minimum of a total of 792 observed implant insertions. There will be approximately 10 providers per supervisor. So, assuming approximately 10% of insertions can be observed (and client acceptability measured through exit interviews), this equals 812 insertions, which is sufficient according to the sample size calculation.

#### Acceptability of Community Health Extension Worker Implant Provision to Health Staff, Facility Managers, and Policy Makers

Approximately 3 to 5 interviews with providers from each cadre will be conducted, until no new information or opinion is yielded from each subsequent interview. Views from the north and south, urban and more remote locations, and different ethnic and wealth contexts will be included; if views are already known, a mix of supporters and opponents of CHEW implant provision will be interviewed.

### Data Collection

#### Safety—Days 0 and 14

At the time of insertion, the provider will record baseline data about the implant insertion, the occurrence of adverse events, and the client’s background (including demographics, socioeconomic information, reproductive history, and reasons for getting an implant). At day 14 post insertion, the provider will ask the client about side effects or complications arising from the procedure.

To assess the ongoing safety of the study, any participant coming to the facility with complaints about her implant up to 30 days after the procedure will be asked a few questions by the provider about what the participant has experienced and her responses will be documented. Responses will be reviewed by project staff.

#### Quality of Implant Provision

Each provider will be visited by her clinical supervisor at 0 (accreditation), 1, 2, 3, and 6 months post training. During these 1 to 2 day long visits, all implant insertions will be observed, and data on quality recorded. Visits will be scheduled in advance and previsit FP demand-generation activities will be conducted by MSION and health care workers. The quality assessment tool includes clinical and nonclinical dimensions, including cleanliness, infection control, taking a client-focused approach, and being responsive to client needs. The tool comprises a checklist of 28 items, observed by the clinical supervisor. For each item, the supervisor will assess provider competence (ie, the provider knows the steps for the skills and can perform them correctly or needs further follow-up) and support to achieve competency (ie, the provider does not know the steps for the skills and does not perform them correctly). The number of items marked “competent” will be totaled to give the provider a score.

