#### Clinical Supervisor Training

A total of 12 clinical supervisors (qualified nurses or midwives with extensive experience of implant service provision) will be trained over 3 days. Training will cover how to train study providers to provide implants, clinical supervision of study providers, and the research study and data collection procedures.

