#### Provider Training in Implant Provision and the Research

Clinical supervisors will train providers on counseling and on insertion and removal of Implanon Classic and Jadelle. Training will comprise classroom and clinic components and include a written test. Training will be based on the FMOH’s competency-based training package for LARCs. This involves working with providers at different levels to bring them up to the same level, and so the number of days of training can vary [24]. The implant clinical training materials, previously only used to train nurses and midwives, will be reviewed and adapted if necessary for CHEWs. Training will be free for providers.

All providers will be trained on the study protocol for managing adverse events, which is based on MSI’s adverse event standard operating procedures. The protocol details when to refer clients to a higher-level provider, particularly important for CHEWs who may be working in clinics without a higher-level provider, and adverse event support and reporting mechanisms. Any major adverse event must be reported immediately to the MSION clinical services manager, who will inform the study manager and the MSI medical development team in London within 24 hours. For this study, moderate adverse events will also be reported to the clinical services manager who will inform the study manager. Reportable adverse events are shown in Textbox 1. Other conditions are to be reported if the level of adversity is judged to be persistent or difficult to manage. The clinical services manager will be responsible for ensuring any adverse event reported is managed effectively.

MSION research staff will train providers on the research study, including participant recruitment and consent, data collection, and data storage. Full training (implant provision and research) is expected to take approximately 8 days.

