#### Supervised Provision

After training, the trainee can provide implants to clients at their clinic only in the presence of a MSION clinical supervisor.

The trainee will encourage FP clients to attend on scheduled days when the supervisor is present. Clients will be counseled on the available methods, and if they choose an implant, they will be given the option of Jadelle or Implanon Classic. Supervision visits will take place every 2 weeks but exact timings will depend on the volume of implant clients. After 5 successful supervised insertions of each brand of implant, the trainee is accredited to insert implants without clinical supervision.

Moderate and major adverse outcomes to be reported to ensure participant safety.Moderate level of adverse eventPartial expulsion of implant, putting the woman at risk of pregnancyPain at insertion site continues for more than 1 week and requires further outpatient observation and medical interventionBleeding that does not stop and requires a transfer to receive medical careInfection that persists after 7 days of antibiotic treatment (may require implant removal)Major level of adverse eventComplete expulsion of the implant resulting in pregnancyPalpitations from the local anestheticBleeding that requires hospital care or results in long-term health impactsInfection that requires hospital care or results in long-term health impactsParesthesia that requires hospital care or results in long-term health impactsScarring that requires hospital care or results in long-term health impactsAnaphylactic response to the implant

MSION staff will conduct demand-generation activities in the local area to increase awareness of the range of contraceptive methods available, including implants, to ensure that trainees have sufficient clients. Activities may include in-facility awareness raising on special days such as antenatal care, immunization, and child welfare days, and recruiting designated locals to encourage potential clients in their communities to attend the nearest study facility for FP.

On the basis of MSION’s previous experience of conducting training and supervision of midwives, nurses, and doctors, it is expected that most providers will have been accredited for insertion by the end of their first supervision visit. Additional visits will be undertaken in cases where accreditation of insertion is not achieved within the prescheduled supervision visit.

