#### Acceptability of Implant Provision—Client Exit Interviews

During supervisor visits, clients participating in the study will be interviewed by the supervisor in private, before leaving the clinic. They will be asked to rate 7 aspects of service provision on a 5-point scale, with responses being totaled to give a satisfaction score. They will be asked if they would recommend the service to a friend.

Data collection points are summarized in Table 3.

**Table 3 table3:** Summary of data collection procedures.

Timing of data collection	Who collects data, and how	Data to be collected	Sample size
At the time of procedure	Supervisor (if present), observes procedure	Quality of service provision	792
Immediately post implant procedure	Community health extension worker (CHEW), nurse or midwife who conducted procedure, observes client and asks her questions at clinic	Client background, record of procedure including complications at the time	8125
	Supervisor (if present), conducts exit interview with client	Client satisfaction, completeness of counseling information, critical information provision	792
2 weeks post procedure	CHEW, nurse or midwife who conducted procedure, asks client questions at clinic or by telephone	Complications following procedure	4410
Within 30 days of procedure	CHEW, nurse or midwife who conducted procedure, records client’s problems at clinic	Complications following procedure	All cases reported spontaneously at the facility

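### Quality is scored by each provider's own unblinded nurse or midwife supervisor and compared by a t test with no supervisor term, so the cadre difference may partly reflect rater severity

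*Protocol article*

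**What the plan says.** - **Who scores quality.** Quality of Implant Provision: "Each provider will be visited by her clinical supervisor at 0 (accreditation), 1, 2, 3, and 6 months post training". The instrument is described in the same section: "The tool comprises a checklist of 28 items, observed by the clinical supervisor". Items marked competent are added up to give the provider's score.
- **Who the supervisors are.** The section Clinical Supervisor Training describes them: "A total of 12 clinical supervisors (qualified nurses or midwives with extensive experience of implant service provision) will be trained over 3 days". This is the profession of the comparator group.
- **Their other roles.** Provider Training in Implant Provision and the Research: "Clinical supervisors will train providers on counseling and on insertion and removal of Implanon Classic and Jadelle". Accreditation follows insertions made in a supervisor's presence (Supervised Provision): "After 5 successful supervised insertions of each brand of implant, the trainee is accredited to insert implants without clinical supervision".
- **Exit interviews.** Client Exit Interviews: "During supervisor visits, clients participating in the study will be interviewed by the supervisor in private, before leaving the clinic". The client rates 7 aspects of the service on a 5-point scale.
- **Workload.** The sample size section for quality and acceptability gives about 10 providers per supervisor. It does not say which cadres make up each group.
- **Analysis.** Data Analysis specifies generalized estimating equations for adverse events, to adjust for clustering. For mean quality and acceptability scores it specifies a t test and names no supervisor or provider term.
- **Bias check.** The Discussion compares adverse event rates recorded by supervisors with those recorded by providers. The main limitations it names are lack of randomization and provider self-assessment, not supervisor scoring.

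**The concern.** One person, who knows the cadre and shares the comparator's profession, produces every checklist score for a given provider, and the first scored visit is the accreditation visit. Two kinds of rater effect are possible.

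The first is general severity: some supervisors mark harder than others. If the cadre mix differs between supervisors, part of that variation enters the CHEW versus nurse/midwife difference. A t test on pooled scores cannot separate it from true quality.

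The second is cadre-specific rating: the same supervisor marks one cadre more kindly than the other. It can run in either direction and remains even when every supervisor rates both cadres.

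The t test also sits badly with the plan's own sizing. The quality sample was enlarged by a design effect of 1.8, yet the stated test treats the scores as independent. At stake are two of the three claims in the study title, quality and acceptability. The primary safety outcome is recorded by providers and is not touched.

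**Working it through.** **1. The plan's own figure.** Inputs from the sample size section: 80% expected in each group, limit 10%, power 80%, significance level 5%.

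n per group = (1.645 + 0.842)² × 2 × 0.8 × 0.2 / 0.10² = 198 (one-sided 5%; one-sided 2.5% would give 252). Then 198 / 0.9 = 220, and 440 × 1.8 = 792. All three stated figures reproduce, and none is disputed.

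**2. What 1.8 can absorb.** Observations per provider: 792 / 120 = 6.6. Per supervisor: 792 / 12 = 66. With design effect = 1 + (m − 1) × ICC, a value of 1.8 corresponds to
- ICC = 0.8 / 5.6 = 0.143 if clustering is by provider;
- ICC = 0.8 / 65 = 0.012 if clustering is by supervisor.

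The allowance is ample for provider clustering and thin for rater clustering.

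**3. Worst case (assumed): each supervisor covers one cadre only, six per cadre.** The article gives no rater ICC, so a range is shown. Power starts from the plan's 80%, adds the supervisor component to the 1.8, and uses 792 × 0.9 = 712.8 complete observations (59.4 per supervisor) and the plan's binomial variance.

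| Assumed rater ICC | Design effect from raters alone, 1 + 65 × ICC | Combined, 1.8 + 58.4 × ICC | Power |
|---|---|---|---|
| 0.02 | 2.30 | 2.97 | about 62% |
| 0.05 | 4.25 | 4.72 | about 46% |
| 0.10 | 7.50 | 7.64 | about 33% |

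In points: with an assumed between-supervisor SD of 5, the rater-induced cadre difference has SD 5 × √(2/6) = 2.89 and a 95% range of ±5.7, against a limit of 10.

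**4. Intermediate mix (assumed): half the supervisors have 7 CHEWs and 3 nurses/midwives, the other half the reverse.** The rater-induced SD shrinks by the factor 0.7 − 0.3 = 0.4, so ±5.7 becomes about ±2.3 points. The design effect from raters alone is 1 + (66 × 0.4² − 1) × ICC = 1 + 9.56 × ICC, or 1.19, 1.48 and 1.96 at ICC 0.02, 0.05 and 0.10.

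**5. Even mix.** With 5 and 5 per supervisor the factor is 0, and general severity cancels from the difference.

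**6. Cadre-specific tilt (assumed 3 points), any allocation.** The standard error at the plan's effective 198 per group is √(0.32 / 198) = 0.0402.
- Tilt against CHEWs, true difference 0: power = Φ(0.07 / 0.0402 − 1.645) = about 54%, down from 80%.
- Tilt in favour of CHEWs, true difference −10%: false noninferiority = Φ(0.03 / 0.0402 − 1.645) = about 18%, up from 5%.

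A supervisor term does not change step 6.

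**The case against.** The strongest reply is that nothing shows the supervisors to be unevenly spread over the cadres. A reader might infer that they are, because CHEW-led and nurse-led facilities can lie in different places. The article is silent on allocation, and a condensed article may leave it to the full protocol. Its other figures make mixed groups plausible: 30 of each cadre per state, and 60 providers over 12 local government areas in Kaduna and 23 in Ondo, or 5.0 and 2.6 per area. A supervisor with about 10 providers, if assigned by geography, would cover some 2 to 4 areas. CHEWs may also be drawn from nurse- or midwife-led facilities. This objection stands, and it makes step 3 of the working a worst case and not an estimate.

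Three further replies also stand. First, in the exit interviews the client gives the ratings, in private, so a supervisor's severity does not carry over. Second, the article does not show that a provider's rater was personally her trainer, only that both come from the same pool. Third, a low mark after accreditation is not an admission of error, since the checklist allows for further follow-up and the monthly meetings offer additional training.

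It can also be said that model terms belong in an analysis plan that is not shown. That would answer a silent article. This one names a t test, for an outcome it sized with a design effect, so the stated method can be judged.

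**Conclusion.** The concern holds in a limited form. The facts are stated in the article: one unblinded rater per provider, from the comparator's profession and from the pool that trains providers, with scoring from the accreditation visit on. The stated test has no supervisor or provider term, and the bias check does not reach these scores. It follows that the checklist difference may partly reflect rater severity. It does not follow that it does, nor that supervisors and cadres coincide.

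The size depends on two unknowns, the cadre mix per supervisor and the rater ICC. The design effect from raters ranges from no excess with even mixing to between 2.3 and 7.5 with complete separation (ICC 0.02 to 0.10), against 1.8 allowed. The direction of any bias is not known. The point concerns secondary objectives 1 and 2 only. For acceptability it is confined to courtesy bias and interviewer effects.

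**What to change.** Replace the t test for quality and acceptability scores with a linear model that has cadre and supervisor as fixed effects and standard errors clustered by provider. With it:
- report how many of the 12 supervisors rated both cadres;
- repeat the comparison without the month-0 accreditation visits, as a sensitivity analysis;
- state in the limitations that a supervisor term removes general severity but not cadre-specific preference, so unblinded rating by the comparator's profession remains a weakness.

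This uses data already collected, provided the supervisor is identified on each form. The cost is some loss of precision. Supervisors who rated only one cadre contribute little or nothing to the cadre contrast, and if there are many of them the adjusted interval will be wide. That is itself worth reporting.

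Balanced allocation of supervisors, or exchanging them after accreditation, is no longer possible because recruitment ended in December 2016. Both are options for a future study only, at the price of more travel and less continuity, and neither would remove a preference for one cadre.
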